## Abstract

**Background:**

In India, 3.6 million pregnancies are affected by preterm birth annually, with many infants dying or surviving with disability. Currently, there is no simple test available for screening all women at risk of spontaneous PTB in low income setting, although high resource settings routinely use cervical length measurement and cervico-vaginal fluid fetal fibronectin for identification and care of women at risk due to clinical history. In rural India, where the public health system has limited infrastructure, trained staff and equipment, there is a greater need to develop a low-cost screening approach for providing early referral, treatment and remedial support for pregnant women at risk of preterm birth. There is interest in the use of a salivary progesterone test as a screening tool preliminary evidence from India, Egypt and UK has shown promise for this type of test. The test requires further validation in a low resource community setting.

**Methods:**

The Promises study aims to validate and test the feasibility of introducing a low-cost salivary progesterone preterm birth prediction test in two rural districts in India with high rates of prematurity. It is a prospective study of 2000 pregnant women recruited from Panna and Satna in Madhya Pradesh over approximately 24 months. Demographic and pregnancy outcome data will be collected, and pregnancies will be dated by ultrasound sonography. Saliva progesterone will be measured by ELISA in samples obtained between 24–28 weeks of gestation. The association between salivary progesterone and preterm birth will be determined and the utility of salivary progesterone to predict preterm birth < 34, as well as < 30 and < 37 weeks assessed. Additional qualitative data will be obtained in terms of acceptability and feasibility of saliva progesterone testing and knowledge of PTB.

**Discussion:**

A validated cost-effective saliva test, which has potential for further adaptation to a ‘point of care’ setting will allow early identification of pregnant women at risk of preterm birth, who can be linked to an effective pathway of care and support to reduce preterm birth and associated adverse consequences. This will reduce both economic and emotional burden on the affected women and their families**.**

## Plain English summary

In India, many babies are born too early in pregnancy (a premature birth that occurs 3 weeks or earlier than term birth which is 40 weeks of pregnancy). Many premature babies die at birth but those who survive also can suffer health issues and disability. Doctors would like to be able to test all women in early pregnancy to determine their risk of a premature birth so that they can provide suitable advice and care, but such a test does not yet exist. In rural situations where healthcare is hard to access, a test that could identify which pregnancies are most at risk would be useful for advising women about pregnancy care and their plans for labour and birth. One potential test is the measurement of the pregnancy hormone progesterone in saliva. Saliva can be obtained easily and safely from women. There is some research that indicates that this test might be useful, but it requires further research before it can be used routinely by doctors or midwives. This article describes the Promises study which will collect pregnancy and birth information from 2000 pregnant women in rural India (two districts in Madhya Pradesh). Each woman will have her pregnancy accurately dated using an ultrasound scan and be asked to provide a saliva sample to measure progesterone between 24 and 28 weeks of pregnancy. The results will be analysed to assess whether the level of progesterone in saliva can identify women who are going to have a baby too early.

## Background

The 2012 Global Action Report on Preterm Birth (PTB) estimates that 15 million PTBs occur annually and that one million neonatal deaths result from prematurity related causes each year [1]. There are 12.9 million premature births annually worldwide [2]. Approximately, over 60% of preterm births occur in in Sub-Saharan Africa and south Asia. PTB, especially early PTB (< 34 weeks of gestation) [3], is a major cause of neonatal mortality and contributes to 75% of neonatal morbidity and 70% of neonatal mortality in industrialized countries [4]. In children under five, preterm birth is the second largest direct cause of child deaths [3]. Preterm babies, in addition to being at a higher risk of neonatal mortality, are at an increased risk of post-neonatal mortality, stunting, and long-term neuro-developmental impairment during childhood. For babies who survive, there is an increased risk of disability, which exacts a heavy load on families and health systems [5]. An estimated 70% of PTBs results from idiopathic preterm labour or pre-labour rupture of membranes and the remainder are iatrogenic because of obstetric or medical indications [6]. PTB has high economic and social burden in terms of health care needs, emotional stress on family in case of preterm baby death and hospital stay [7] (WHO 2012). India has the highest number of PTBs and preterm deaths worldwide [5], contributing to 25% of the overall global preterm related death; of a total 27 million babies born annually, 3.6 million babies are born preterm, and over 300,000 of these preterm babies die each year because of associated complications [5, 8]. This is even more challenging in Indian rural setting where most women are unaware of the risk of PTB; and do not readily access available care and support. This leads to increased maternal and neonatal morbidity and mortality in rural India [9]. A systematic analysis of global, regional and national causes of child mortality in 2013 identified PTB birth complications and infections to be the two major causes of neonatal deaths in India [10]. In addition, surviving preterm babies are at greater risk for short-term health complications including acute respiratory, gastrointestinal, infectious, central nervous system, hearing, and vision problems, and long- term neuro-developmental disabilities such as cerebral palsy, impaired learning and visual disorders, as well as chronic diseases in adulthood [11, 12].

Addressing PTBs is essential in order to progress on Sustainable Development Goal (SDG) 3, to reduce the neonatal mortality rate (NNMR) to as low as 12 per 1000 live birth [13] especially in countries with high burden of PTB. Despite the magnitude of the problem, there is no established early pregnancy-screening test or effective treatment for women once a high risk of spontaneous preterm birth (sPTB) is ascertained [14].

In high resource settings, there is the option for mid-trimester risk prediction using transvaginal ultrasound measurement of cervical length measurement and cervico-vaginal fetal fibronectin [14–18] for identification and care of women who are already deemed to be at risk due to clinical history (previous PTB, previous mid-trimester miscarriage or premature rupture of membranes). These tests for predicting PTB risk are invasive, expensive, require skilled workforce and facilities and are not feasible for rural Indian setting where such facilities are largely unavailable or scarce. Development of an acceptable, non-invasive, ‘point of care’ test for accurate prediction of women at risk of early PTB has considerable potential to reduce infant deaths in low-resource settings through improvements in antenatal and postnatal care uptake and or by referral of high risk women to higher level health facilities with experience in care of vulnerable infants. A small study in the UK has indicated that salivary progesterone concentrations are significantly lower from 24 weeks of pregnancy in women, who had a spontaneous PTB (< 34 weeks gestation) [19]. This highlighted the potential of using salivary progesterone measurements for the prediction of early preterm labour and determining specific women that might benefit from intervention [12, 20–25]. Subsequently, two further studies have confirmed the predictive potential of salivary progesterone measurements in urban populations in India (high risk women) [26] and Egypt [27] (high risk and low risk women). Both indicated that salivary progesterone can identify women destined to deliver < 34 weeks with a sensitivity, specificity, positive and negative prediction values of 83–84%; 86–90%, 60–89.8% and 85.9–95% respectively. With this backdrop, our study aim is to assess and validate the use of a non-invasive salivary progesterone test in a community setting where there is limited or no routine intervention for PTB, to obtain definitive evidence to support the widespread introduction of salivary progesterone testing for PTB in India.

## Methods/design

### Hypothesis and aims

In India, there is a clear need to introduce some form of antenatal screening for PTB if there is to be a reduction of PTB and associated neonatal mortality. Saliva testing of progesterone, which reflects the unbound, unconjugated biologically active fraction of the plasma hormone level profile, has benefits over using a more invasive blood test. We hypothesised that successful validation of the salivary progesterone test could provide an inexpensive, easy to use, non-invasive and acceptable test for early detection of risk of PTB among pregnant women in rural India.

### Study objectives

To determine the association and assess the performance of a salivary progesterone test (specificity, sensitivity, predictive value and ROC) for prediction of PTB risk at < 34 weeks and < 37 weeks of gestation.To assess the feasibility, and acceptability to women and health care workers, of this test in a rural setting.

As part of objective two, the goal is to gain a fuller understanding of the range of facilitating factors and barriers influencing the use of salivary progesterone PTB tests in Indian rural settings.

### Study sites

This study will be carried out in the state of Madhya Pradesh, India (Fig. 1). The NNMR of Madhya Pradesh is 34, which is quite higher than the national average [28]. Two districts (Panna and Satna) with high fertility (Crude Birth Rate: 31.3 and 28.2respectively) and high rates of NNMR (61–57 per 1000 live births) [29] particularly resulting from births < 34 weeks [30] and an infant mortality rate of 85 per 1000 live births were selected. Major contributors to PTB/neonatal mortality [21] in these tribal dominated districts are poverty, physical stress, malnutrition, poor public health facilities and low health service utilization. Two blocks each covering more than 100,000 populations will be included from each district.

**Fig. 1 Fig1:**
[figure not shown]
Location of study districts (Panna and Satna) in the state of Madhya Pradesh, India

### Study design

A prospective observational cohort study to recruit 2000 pregnant women from the two districts of Madhya Pradesh (Fig. 1). The flow of participants through the study is shown in Fig. 2. Mapping was conducted by the field staff to identify areas that had comparable population density and somewhat comparable geographic size, with natural boundaries noted.

**Fig. 2 Fig2:**
[figure not shown]
Process Flow Chart of the Project

Based on the PTB rates in two study districts (~ 23%), it was estimated that recruitment of 2000 women would identify ~ 460 preterm deliveries at < 37 weeks’, providing ample power to predict PTB at this gestation. Evidence suggests that the salivary progesterone test works best to detect birth < 34 weeks [19], but the incidence for this gestation is not known for the study districts. However, if 189 cases of PTB < 34 weeks’ are identified (9.5% incidence), this would provide 90% power to distinguish 80% from 70% sensitivity. Pregnant women will be identified and consented early in pregnancy so that an accurate dating scan can be achieved, and baseline obstetric history and demographic data obtained. Women will then be asked on a subsequent visit to provide a saliva sample between 24 and 28 weeks of pregnancy. Women will be followed-up till delivery for birth outcomes.

### Study duration

The study will be conducted for a period of 24 months. The major activities to be conducted include project planning, gaining of ethical approval, training of frontline functionaries and laboratory technicians, line listing and recruitment of pregnant women, salivary sample collection, storage and transportation and batch analysis of saliva progesterone.

### Inclusion & Exclusion criteria at time of recruitment

Inclusion Criteria:

1. Women whose pregnancy is confirmed will be registered.

2. Women with singleton pregnancy.

3. Pregnant women whose gestation period is established by ultrasound scan.

Exclusion criteria:Pregnant women unwilling or unable to give informed consentWomen unable to give informed consentPregnancy not dated by ultrasound (or by late ultrasound > 20 weeks).Failure to confirm viable intrauterine pregnancy by ultrasound scanWomen with multiple pregnancy

Demographic and pregnancy outcome data will be retained for women whose pregnancies are only dated by last menstrual period as this will still contribute to understanding of clinical factor and PTB.

At the time of saliva collection, women are consented for the provision of a saliva sample for progesterone analysis. Women unable or unwilling to provide a saliva sample will be retained in the study for clinical data collection.

### Ethics committees review and approval

Ethical approval was granted by the MAMTA Health Institute for Mother and Child (MAMTA-HIMC) Ethical Review Board (MERB/Dec-2016/002) and the Institutional Review Board of Mahatma Gandhi Institute of Medical Science (MGIMS/IEC/OBGY/289/2016). As the project included sample analysis, written (Hindi or English), signed (or with thumb impression, if illiterate) and informed consent is required from each eligible pregnant mother both at study entry and the time of salivary sample collection.

A confidential ID will be given to each participant and inserted in consent forms, test forms, questionnaires and sample collected for the purpose of data linkage and analysis.

### Training and knowledge of field staff

Before the recruitment of participants and sample collection, training involving practical sessions will be provided for study staff including district coordinators and outreach workers and the laboratory teams responsible for saliva sample collection and saliva testing (sample storage and immunoassay at the health facility).

### Research tools

A package of research tools has been developed, translated in Hindi language and pre-tested for data collection. The research tools consisting of structured questionnaires and semi-structured in-depth interviews are: a) A tracking tool designed for recruited pregnant women to obtain information on their demographic details, and previous pregnancies and follow their current pregnancy including antenatal care visits, Ultra sonography (USG) scan details and post-natal tracking for delivery outcomes along with documentation of saliva sample collection, storage and transportation details, analysis process and progesterone results. b) Pre-post training assessment tool for frontline functionaries to determine the effectiveness of training on the knowledge on preterm birth. c) In-depth interview (for pregnant women and frontline functionaries on knowledge of preterm birth, accessibility to relevant antenatal care, and the perception of the test and its usefulness.

### Recruitment and consent process of pregnant women

Women will be identified as early in pregnancy as possible (ideally < 12 weeks’ of gestation). The list of eligible pregnant women will be obtained from the local Accredited Social Health Activist (ASHA) workers and the local awareness campaigns by the study’s outreach workers (ORW). They will establish rapport with the pregnant women and family members. The outreach workers will provide information to pregnant women about pregnancy health care, PTB and the importance of PTB screening. Any woman appearing as needing medical attention will be encouraged to attend their local health facility by the ORW.

All participants will be provided with a participant information sheet (PIS) with verbal translation available for local language speaking women. Women will be consented by an appropriately trained study staff (i.e. district coordinator or outreach worker). They will be provided information about the study and will be allowed adequate time to read the participant information sheet and provide written informed consent. Where there is doubt about the ability of a volunteer to provide informed consent, they will not be recruited. In case of potential recruits have impaired hearing, the outreach workers (ORW) along with frontline workers will make every effort to ensure that her answers to any queries are fully understood and may consider asking a member of the family to attend the discussion prior to the signing of the consent form. In case of illiterate women or the women with inability to understand the concept of informed consent the outreach workers would read the information sheet to the volunteer in the presence of a literate witness which may be the frontline workers (ASHAs), preferably. The consent form should also be read to the literate witness prior to signing or making a mark and countersigned by the literate witness. The consent form will be filed in the participants’ consent form file in study number order and stored in a locked filing cabinet at the District Outreach office separated from study data.

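### The witnessed consent route takes in women who cannot understand informed consent, although the exclusion list and the doubt rule bar them

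*Protocol article*

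**What the plan says.** Four statements in the protocol article bear on who may consent and how.

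- **Inclusion & Exclusion criteria at time of recruitment.** Women who are unable to give informed consent are excluded. The list says so twice, once together with unwillingness and once alone.
- **Recruitment and consent process of pregnant women, doubt rule.** "Where there is doubt about the ability of a volunteer to provide informed consent, they will not be recruited". No exception is attached.
- **Same section, two sentences later, witness route.** The group is defined by the words "illiterate women or the women with inability to understand the concept of informed consent the outreach workers would read the information sheet", and the reading takes place before a literate witness, preferably a frontline worker. The procedure ends with a completed form: "The consent form should also be read to the literate witness prior to signing or making a mark and countersigned by the literate witness".
- **Ethics committees review and approval.** Consent must be written, and "signed (or with thumb impression, if illiterate) and informed consent is required from each eligible pregnant mother", both at study entry and when saliva is collected. Illiteracy is the only ground given for a thumb impression.

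**The concern.** The witness sentence joins two different groups with the word *or*. A woman who cannot read can be fully able to decide once the sheet is read to her, and a literate witness can attest that the reading matched the text. A woman who cannot understand what consent is has a different difficulty, and the presence of a literate person does not supply the understanding she lacks. In ordinary meaning she is unable to give informed consent, or at the least her ability is in doubt. The exclusion list and the doubt rule keep her out, while the witness sentence takes her through to a signed or marked form.

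Two things are at stake. The first is participant protection: the text offers a way to a form that is complete on paper without the understanding that makes it valid. The second is a uniform eligibility rule. Consent is taken by outreach workers or district coordinators, largely on household visits, and two of them could treat the same woman differently depending on which sentence they follow.

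**Working it through.** No arithmetic applies. The check is to take each kind of woman the text distinguishes and ask what each rule says about her.

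| | Exclusion list | Doubt rule | Witness route | Thumb impression (ethics section) |
|---|---|---|---|---|
| Cannot read or write, understands the study | Not barred | Not barred | Covered | Allowed |
| Can read, does not understand the concept of consent | Barred | Barred | Covered | Not provided for |
| Cannot read, does not understand the concept of consent | Barred | Barred | Covered | Allowed as to form, but consent must still be informed |

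1. **First row.** All four statements agree. The procedure fits the need: reading aloud overcomes illiteracy, the mark replaces the signature, and the countersignature documents both.
2. **Second row.** The exclusion list and the doubt rule say no. The witness route names her group and leads to a completed form. The ethics section gives no ground for a mark, because she is not illiterate.
3. **Third row.** The conflict between the exclusion list and doubt rule on one side and the witness route on the other is the same. The thumb impression is available to her because she is illiterate, but the ethics section still requires that the consent be informed.
4. **Is the difference only one of terms?** The exclusion list speaks of being unable to *give* consent and the witness sentence of inability to *understand the concept*. For these to describe different women, there would have to be women who do not grasp the concept and can nevertheless give informed consent. The text does not describe such a group.
5. **Does the witness route contain its own stop?** It sets out the reading, the witness, the signature or mark, and the countersignature. It states no check of understanding after the reading, and no instruction to stop if understanding is not reached.

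The rows for women who do not understand therefore contradict each other across the sections. The row for illiterate women who do understand is sound and should be left as it is.

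**The case against.** The strongest reply is that the sentences can be read together. The doubt rule comes first and is unconditional. What follows is a list of aids to communication, first for impaired hearing and then for illiteracy or unfamiliarity with consent. On that reading the second group means women who need the idea explained orally, and anyone still unable to consent afterwards falls back under the doubt rule and the exclusion list. Other safeguards point the same way: staff taking consent are to be appropriately trained, eligibility criteria are to be checked thoroughly and queries answered at the first household visit, and a second consent is taken before saliva is collected. The article is also condensed, and the consent form and full consent procedure are not shown.

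This is a possible reading and may be what the authors meant. It does not settle the matter, because the text says inability to understand, not need for explanation, and it does not send the woman back to the doubt rule after the reading. General training and eligibility checks cannot resolve two instructions that point opposite ways. Condensation does not explain it either: nothing is missing here; both rules are stated and they conflict.

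What stands of the reply limits the point. A reader might infer that staff *would* enrol barred women, that some definite share of the 2000 women is affected, or that data and saliva would have to be withdrawn. The documents support none of these. The witness sentence does not tell staff to set the criteria aside. No figure is given from which a number of women could be derived. Withdrawal is conjecture, and saliva in particular cannot be taken on the first consent alone. It is also fair to say that a literate woman who is merely unfamiliar with consent, and understands once told, should not lose the chance of an explanation; the fix should keep that open.

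**Conclusion.** The contradiction is in the current text and should be corrected. The exclusion list and the doubt rule bar women who are unable to give informed consent or whose ability is in doubt. The witness sentence, read literally, gives women who cannot understand the concept a route to a completed form, and the ethics section does not support extending a mark beyond illiteracy. Staff *could* therefore enrol women without valid consent.

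The number of women concerned is unknown. No sample size, power or error rate is affected, and nothing in the documents shows that any woman has been wrongly enrolled. The conclusion rests on one assumption, the ordinary meaning of the words: that a woman who cannot understand the concept of informed consent is unable to give it, or is at least in doubt. If the authors meant only women who need an oral explanation, the wording still has to be changed to say so.

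**What to change.** Reconcile the exclusion list, the ethics section and the recruitment section as follows.

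1. In the recruitment section, limit the witnessed sign-or-mark route to women who cannot read or write but understand the study, and delete from the witness sentence the second group, those unable to understand the concept of consent. The route then matches the ground that the ethics section gives for a thumb impression.
2. Add that the information sheet may be read and explained to any woman who needs it, and that a woman whose understanding is still in doubt afterwards is not recruited.
3. State that the same check applies at both consents: at study entry and at saliva collection.
4. In the exclusion list, remove the duplicate item so that the criterion appears once.

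The cost is one deleted clause, two short added sentences and a note to the outreach workers and district coordinators. The route for illiterate women stays intact, and no analysis changes.
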